## Sample size calculation and statistical analysis

The sample size, with a minimum of 20 participants for each individual genotype and *n* = 20–22 for each individual genoset, is based on previous work performed by this research group [13]. A power calculation was performed using PROC POWER SAS Institute (version 9.4) using the paired means statement to model the AB/BA crossover design (corr = 0.75, a = 0.05 and b = 0.80); based on an average reduction in LDL-C of 0.34 mmol/L resulting from PS consumption according to the meta-analysis findings of Demonty et al. [8], the standard deviations in LDL-C for placebo (0.67 mmol/L) and PS (0.7 mmol/L) from the MacKay et al. [11] and a correlation in LDL-C values of 0.75, which was an estimate based on variability in LDL-C concentrations over time from MacKay et al. [11] and on a within-persons correlation in cholesterol response to plant sterols [15]. From this power calculation, we determined that 18 participants would be needed for each genoset to detect a response, in the form of a significant reduction in LDL-C from placebo to plant sterol consumption period, in the group. Our objective was to test if each genoset would respond, with the hypothesis that the *CYP7A1 rs3808607T/T* and *APOE E3/3* genoset would not respond to plant sterol consumption with LDL-C lowering.

Given the crossover design, the study outcomes measures will be analyzed in a per-protocol population where only participants who received both treatment and placebo are included. The effects of treatment, comparing the endpoint values of the treatment and placebo periods, will be analyzed by the SAS MIXED procedure. Sequence and sex will be included in the model as fixed factors, while participants will be included as a random and repeated factor. Genoset and treatment by genoset will be included as fixed factors to assess the impact of the genoset on the treatment. The impact of the individual genotypes will also be investigated individually. Significant treatment-by-genoset or treatment-by-genotype effects will be examined by the SAS SLICE function, with Bonferroni correction for the number of slices. Treatment effect sizes by genoset or genotype, from significant interactions, will be compared by t test or ANOVA using the difference in mixed-model least squares means summary statistics for the treatment effect slices, with Tukey-Kramer adjustment for multiple comparisons [13].

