## Methods/Design

### Study design

To formally validate whether *APOE isoform*, which is formed by *rs7412* and *rs429358,* and *CYP7A1 rs3808607* can predict responsiveness to PS consumption across the general population, the present proposal is to carry out a double-blind, placebo-controlled, randomized two-period crossover study to investigate the LDL-C responsiveness to the controlled administration of PS. The PS treatment will consist of two daily single portions of margarine, providing 1 g each of PS during the PS period (2.0 g/day of PS in total). The placebo treatment will be an identical margarine, except it will not contain any added PS. Both the PS and placebo margarine treatments will be coded by the industrial partner organization, Unilever, and provided to the research group to maintain blinding of both the researchers and participants throughout the clinical trial.

We have two original specific hypotheses. 1) *APOE isoform* and *CYP7A1 rs3808607* will independently predict the response to PS consumption in a pattern that reflects the current gene-biomarker associations as outlined in Table 1. *APOE ε4/−* will be more responsive to PS than *ε3/ε3*. The *CYP7A1 rs3808607* G allele will predict responsiveness to PS consumption in a dose-responsive fashion, with T/T predicting nonresponse. 2) The genosets formed by combinations of *APOE isoform* and *CYP7A1 rs3808607* will follow the pattern as predicted in Table 2.

**Table 2 Tab2:** Original plant sterol trial genotype recruitment targets and predicted response

ApoE	CYP7A1	Predicted response	Planned recruitment
ε2/−	T/T	Nonresponder	*n* = 8
ε2/−	G/−	Responder	*n* = 8
ε3/ε3	T/T	Non-responder	*n* = 8
ε3/ε3	T/G	Responder	*n* = 8
ε3/ε3	G/G	Responder	*n* = 8
ε4/−	T/T	Responder	*n* = 8
ε4/−	T/G	Responder	*n* = 8
ε4/−	G/G	Responder	*n* = 8

Because of the amount of time spent on recruitment and the difficulty in finding participants who were eligible with rare combinations of genosets, the APOE 2 groups were removed, and other groups were combined. To maintain the study power, we increased the *n* in the other groups as described in Table 3.

**Table 3 Tab3:** Amended plant sterol trial genotype recruitment targets and predicted response

ApoE	CYP7A1	Predicted response	Planned recruitment
ε3/ε3	T/T	Nonresponder	*n* = **20**
ε3/ε3	G/−	Responder	*n* = 22
ε4/−	−/−	Responder	*n* = 22

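### The 18 per genoset at 80% power applies to one uncorrected within-genoset test, not to the interaction-gated, Bonferroni-corrected slices that are planned

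*Protocol article*

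**What the plan says.** All of this is in the protocol article.

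- **Power calculation** (Sample size calculation and statistical analysis): "A power calculation was performed using PROC POWER SAS Institute (version 9.4) using the paired means statement to model the AB/BA crossover design", with "corr = 0.75, a = 0.05 and b = 0.80". The value labelled b is read here as power. The effect is "based on an average reduction in LDL-C of 0.34 mmol/L resulting from PS consumption". The SDs are 0.67 mmol/L on placebo and 0.70 mmol/L on plant sterols, with "a correlation in LDL-C values of 0.75, which was an estimate based on variability in LDL-C concentrations over time". The result: "From this power calculation, we determined that 18 participants would be needed for each genoset to detect a response". The sentence goes on to define response as a significant fall in LDL-C from placebo within the group, and the stated objective is to test whether each genoset responds.
- **Analysis** (same section): a mixed model with genoset and treatment by genoset as fixed factors. Significant interactions are then examined by slices, "with Bonferroni correction for the number of slices".
- **Recruitment** (Study design, Table 3): 20, 22 and 22 in three genosets, one predicted nonresponder and two predicted responders. After the ε2 groups were dropped, the other groups were enlarged: "To maintain the study power".
- **Use of the result** (Discussion): a genoset that does not reach a significant LDL-C reduction is classed as nonresponder.

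**The concern.** The test that was powered is a single paired comparison in one genoset at α = 0.05, with nothing to pass beforehand. The analysis described in the next paragraph puts an interaction test in front of that comparison and lowers its α. Neither step enters the power calculation, although both are written in the same section.

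Power has a direct consequence in this trial, because the classification rule turns non-significance into a label. If a genoset that truly responds misses significance, it is called nonresponsive, and the Discussion foresees different advice for such people. Someone who takes 80% as the chance of detecting a responding genoset under the planned procedure would be relying on a figure that was not calculated for it.

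**Working it through.** **Inputs from the protocol.** δ = 0.34 mmol/L; SDs 0.67 and 0.70; correlation 0.75; α = 0.05; 18 per genoset stated; 20/22/22 planned.

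**Assumptions.** Two-sided testing (not stated, but a one-sided t test would give 15, not 18). Three slices, one per genoset in Table 3. The nonresponder genoset has effect 0, as hypothesised, and both responder genosets have 0.34. Sex and sequence terms are ignored.

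**1. The stated figure.**
Variance of the paired difference = 0.67² + 0.70² − 2 × 0.75 × 0.67 × 0.70 = 0.4489 + 0.4900 − 0.7035 = 0.2354, so SD = 0.4852.
Standardised effect = 0.34 / 0.4852 = 0.701. At n = 18 the noncentrality is 0.701 × √18 = 2.97.
Two-sided t test, 17 df: power 80.0% (n = 17 gives 77.4%). The stated 18 is confirmed.

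**2. A corrected slice.** α = 0.05/3 = 0.0167, noncentrality 0.701 × √n. Power depends on whether the error df are the genoset's own (n − 1) or pooled over genosets.

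| n | Own df | Pooled df |
|---|---|---|
| 18 | 63% | 69% |
| 20 | 69% | 75% |
| 22 | 75% | 79% |

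Reaching 80% takes 25 per genoset on own df, or 23 with pooled df.

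**3. The interaction.** On within-person differences this is an F test with 2 and N − 3 df and noncentrality λ = Σ nᵢ(δᵢ − δ̄)² / 0.2354.
At 20/22/22 with effects 0/0.34/0.34:
δ̄ = 44 × 0.34 / 64 = 0.23375.
Σ nᵢ(δᵢ − δ̄)² = 20 × 0.23375² + 44 × 0.10625² = 1.0928 + 0.4967 = 1.5895.
λ = 1.5895 / 0.2354 = 6.75. Power on F(2, 61) = 62%.
At 18 each: λ = 5.89, power 55%. Reaching 80% takes about 31 per genoset.

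**4. Sensitivity of the interaction at 20/22/22.**

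| Nonresponder effect | Responder effects | Power |
|---|---|---|
| 0.17 | 0.34, 0.34 | 19% |
| 0.10 | 0.34, 0.34 | 34% |
| 0 | 0.34, 0.34 | 62% |
| 0 | 0.42, 0.42 | 81% |
| 0 | 0.49, 0.49 | 92% |

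The last row is what follows if 0.34 were the average over this trial's own mix: 0.34 × 64/44 = 0.49.

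**5. Gate and slice together.** With 200,000 simulated trials at 20/22/22, effects 0/0.34/0.34 and pooled error, the interaction and one given responder slice are both significant in about 53%.

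**The case against.** The strongest defence is that the protocol says what the 18 is for: a within-group reduction, matching an objective of testing whether each genoset responds. It nowhere claims 80% power for a difference between genosets. That stands. A reader might infer an arithmetic error, or a false claim about the interaction, and the text supports neither. Likewise, the remark on maintaining study power explains larger groups after the ε2 groups were removed; it does not mention a comparison between genosets.

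Second, recruiting 20–22 rather than 18 nearly absorbs the correction. The slices come from one mixed model, so pooled error is the closer match, and at n = 22 a responder slice then has 79%. The genoset of 20 is the predicted nonresponder, where power to detect a response is not the hypothesis. This also stands: the slices alone do not show a serious shortfall at planned recruitment. The n = 18 rows show what the stated minimum delivers. They are not a forecast, because no dropout rate is given.

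Third, the documents give no genoset-specific effects, and 0.34 is an average from a meta-analysis. Hence 62% is conditional and cannot be quoted without its range.

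Fourth, one could compute the chance that the interaction and both responder slices are all significant and call it the power of the trial. No section defines success that way, so that figure is not used here.

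What the defence does not answer is the gate. The objective calls for a test in each genoset, but the analysis as written reaches those tests only through a significant interaction.

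**Conclusion.** The concern holds as a mismatch between the powered test and the planned tests. The 18 at 80% is correct for one uncorrected, ungated two-sided paired test within a genoset, and for nothing else in the plan.

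The correction alone costs little at planned recruitment: 75–79% at n = 22. The gate is the larger part. Under 0/0.34/0.34 the interaction has about 62%, and a truly responding genoset clears both gate and slice in about 53% of trials. The result is sensitive in both directions: a partial response in the predicted nonresponders lowers interaction power to 34% or 19%, and responder effects of 0.42 or more raise it above 80%. It would be too strong to conclude that the trial is underpowered whatever the truth, since the documents do not fix the effects by genoset.

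The figures rest on three slices, two-sided tests and the protocol's own SDs and correlation. Should-fix: the power statement needs restating, but the design does not have to change.

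**What to change.** In the sample size section:

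- State that 18 per genoset with 80% power refers to a single within-genoset paired test at α = 0.05, without Bonferroni correction and without a prior interaction test.
- Report power at 20/22/22 for the tests to be run: 75–79% for a corrected responder slice at n = 22 (own to pooled df), and about 62% for the interaction if the effects are 0/0.34/0.34 mmol/L. Give the 19–92% range and the assumption behind each value.

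In Study design, make clear that the study power being maintained is that of the within-genoset test.

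The cost is a less favourable stated figure. No participants are added, and neither the design nor the analysis changes.

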**Fig. 1 Fig1:**
[figure not shown]
Schematic flow diagram of the trial protocol

Participants will be required to attend breakfast at the RCFFN or Seven Oaks General Hospital (SOGH) and consume a meal containing one daily portion of margarine under supervision from Monday to Friday; the additional daily portion will be consumed with their evening meal. Participants will be given their evening and weekend margarine portions to take home for consumption. Participants will be provided diaries in which they are instructed to record when they ate the margarine in the evenings and on the weekends. During the week, participants will be required to return the empty margarine tubs on the following day to help monitor compliance, with those margarine tubs used on Saturday and Sunday being returned on Monday. The return of the empty tubs and the record of the consumption in the study diaries will be verified by clinical coordinators using a compliance checklist. Additionally, serum noncholesterol sterols, including sitosterol and campesterol, the two main PS in the margarine, will be measured to monitor compliance. Partial supervision of treatment consumption in person and the monitoring of unsupervised treatments by return of the empty container represent a compromise between participant compliance and participant burden.

Missed treatment consumption and return of margarine tubs will be recorded for each participant. Noncompliance of a participant will be defined as 1) missing supervision, 2) failing to return at least 80% of the total empty margarine tubs per treatment period, and 3) missing two consecutive measurements or blood sampling days. Noncompliant participants will be asked to leave the trial; however, they will be compensated on a prorated basis according to the duration of their involvement in the trial. Participants were asked to maintain their typical diet and physical activity levels throughout the study.

Additionally, on a weekly basis, clinical coordinators will ask participants to report any changes in diet, lifestyle (sleep), or physical activity, which may interfere with the results of the trial and any other health outcomes or symptoms they may experience during the trial. Fasting blood samples are collected from participants on 2 consecutive days at the beginning (Days 0 and 1) and at the end (Days 28 and 29) of each trial period as described in the Table 4.

**Table 4 Tab4:** Schedule of enrollment, interventions, and assessments

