### Randomization

Eligible participants will be randomly allocated to two groups: the PS treatment group or the placebo group for the first period, and then, participants will switch treatments for the second period after the washout between periods. Randomization will be done by an assistant outside of the research team using a block randomization method through sealed envelopes with stratification by sex and genoset. Randomization in blocks of eight and four, each with equal numbers of treatment orders will be used. This blocking is being done to minimize imbalances in treatment orders within each genoset group or by sex. Administration of the intervention will be conducted in a double-blind manner. Single portion tubs of PS treatment and placebo margarine are being created for this study by Unilever and are being delivered to the research team in identical packages labeled either A or B.

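### The only stated analysis set is a both-treatments per-protocol population, fed by removal after randomization under an ambiguous noncompliance rule, in a model that lists no period effect

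*Protocol article*

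**What the plan says.** Under Sample size calculation and statistical analysis, the article gives the crossover design as its reason and states that "the study outcomes measures will be analyzed in a per-protocol population where only participants who received both treatment and placebo are included". No all-randomized or sensitivity set appears. The same paragraph compares endpoint values of the two periods in SAS MIXED. Sequence and sex are fixed factors, participant is a random and repeated factor, and genoset and treatment-by-genoset are added as fixed factors. Period is not in the list.

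In Methods/Design, Study design (text below Fig. 1), the first two items of the noncompliance definition read "1) missing supervision, 2) failing to return at least 80% of the total empty margarine tubs per treatment period". The list then closes, after a comma, with a third item: "and 3) missing two consecutive measurements or blood sampling days". The consequence is that "Noncompliant participants will be asked to leave the trial".

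Genotyping is done on the screening sample, and randomization is by blocks "using a block randomization method through sealed envelopes with stratification by sex and genoset". Table 3 plans 20 participants in ε3/ε3 T/T and 22 in each of the other two genosets. The power calculation asks for 18 per genoset. The Discussion section classifies genosets that do not reach a significant LDL-C reduction as nonresponders.

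**The concern.** A crossover makes a both-periods analysis natural but does not require it. The planned mixed model has a participant effect and can use a participant with one period endpoint. As written, whether a randomized participant contributes depends on what happens after randomization: dropping out before the second product, or being asked to leave. Either may be related to tolerance of the product or to adherence, and randomization does not protect against that. Once a participant has left, the later day 28 and 29 samples may never be drawn, so no later reanalysis can recover them.

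The removal rule is not fixed well enough to tell which participants will leave. Two coordinators could apply it in good faith and end up with different populations.

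What is at stake is the genoset label. It is decided by significance in groups of 20 to 22, and the stated aim is prediction across the general population.

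**Working it through.** **1. The plan's own figure.** Inputs from the sample size section: mean reduction 0.34 mmol/L, SD 0.67 (placebo) and 0.70 (plant sterol), and "corr = 0.75, a = 0.05 and b = 0.80" (0.80 is read as power and alpha is taken as two-sided).

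SD of the within-person difference = √(0.67² + 0.70² − 2 × 0.75 × 0.67 × 0.70) = √(0.4489 + 0.4900 − 0.7035) = √0.2354 = 0.485.

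With a paired t test (noncentral t), the first n with power of at least 0.80 is 18 (power 0.800). The stated 18 reproduces.

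**2. Margin.** ε3/ε3 T/T: 20 − 18 = 2, or 10%. Each other genoset: 22 − 18 = 4, or 18%.

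**3. Chance of a false nonresponder label if the true effect is 0.34** (1 − power, at the plan's unadjusted 0.05):

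| n analysed | power | false label |
|---|---|---|
| 22 | 0.88 | 12% |
| 20 | 0.84 | 16% |
| 18 | 0.80 | 20% |
| 16 | 0.75 | 25% |

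This is the effect of smaller numbers alone. It assumes that losses are unrelated to response.

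**4. The noncompliance rule, read both ways.** Two tubs a day for 28 days is 56 per period. 80% of 56 is 44.8, so at least 45 must come back and 11 may be missing. Weekday breakfasts number 20 per period, 40 over both.

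- Read literally ('and'): a participant who returns no tubs at all is still compliant unless they also miss supervision and miss two consecutive measurements or sampling days.
- Read as 'any': one missed breakfast of 40 suffices, because the first item has no threshold, although the second item tolerates 11 unreturned tubs of 56.

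**5. Sequence imbalance without period in the model.** Let δ be the period 1 minus period 2 difference. The within-person contrast (plant sterol minus placebo) has expectation τ + δ in the plant-sterol-first sequence and τ − δ in the other. With n₁ and n₂ completers, the genoset estimate has expectation τ + δ(n₁ − n₂)/(n₁ + n₂). A fixed sequence factor works between participants and does not remove this term.

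- 10 and 10: no leak.
- 10 and 8 (both losses from one sequence of ε3/ε3 T/T): 2/18 = 11% of δ.
- 11 and 7 (all four losses from one sequence in a genoset of 22): 4/18 = 22% of δ.

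The documents give no value for δ. With period in the model, the leak is removed.

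**6. What one-period participants add.** Generalized least squares with correlation 0.75, equal variances, variance components treated as known, and treatment, sequence and period fitted: adding two period-1-only participants (one per sequence) to 18 completers lowers the standard error by 0.6%, worth about 0.23 of a completer. Adding four lowers it by 1.1%, about 0.42 of a completer.

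**The case against.** The strongest reply is that the both-treatments set suits the question asked. The contrast is within-person and the aim concerns response to controlled administration, so people who took both products are a defensible population. This stands in part. Step 6 shows that one-period participants hardly improve precision, so admitting them does not restore the margin over 18. Someone removed before the first endpoint would still contribute nothing. It does not answer selective loss or the missing period term.

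A second reply is that thresholds, and perhaps a sensitivity set, may sit in the full protocol or an analysis plan that is not shown. That is fair for detail. But the article states the population and the rule affirmatively, and the rule as stated supports two very different readings.

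Four stronger readings are tempting, and the documents do not support them:

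- *The rule contradicts itself.* It does not: the three items can all be true of one person. It is ambiguous.
- *Exclusions move people between genosets.* They cannot: genoset is genotyped at screening and is a randomization stratum.
- *The analysed set holds only people who never lapse.* The stated criterion is receipt of both products, and adherence enters only through the removal rule.
- *A large share will be removed.* Under the 'any' reading the share is 1 − (1 − p)^40 for a per-breakfast miss probability p. The answer runs from 18% at an assumed p of 0.5% to 55% at 2%, with independence also assumed. No p is given, so these figures reflect the assumption and not the trial.

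**Conclusion.** The point holds in a limited form. The genoset classification rests on one set shaped after randomization, the removal rule cannot be applied consistently as worded, and the listed model lets unequal losses between sequences carry any period effect into a genoset's treatment estimate (11% of it at 10 versus 8).

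The number of losses the plan can absorb before falling below its own 18 is small: 2 in ε3/ε3 T/T and 4 in each other genoset. Fewer participants alone raise the chance of a false nonresponder label in ε3/ε3 T/T from 16% at 20 to 20% at 18, if the true effect is 0.34 and the plan's SDs and correlation hold. That genoset is both the smallest and the one hypothesised not to respond.

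A reader might infer that the results will be biased by a known amount or toward the hypothesis. That does not follow. Without a dropout rate, a noncompliance rate or a period effect, neither size nor direction of bias can be computed. The change is worth making because it is cheap, not because harm has been shown.

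**What to change.** - Add period to the fixed factors of the MIXED model.
- Report an analysis of all randomized participants with at least one period endpoint, as randomized, in that model, alongside the both-periods set, so that the genoset classification does not rest on the per-protocol set alone.
- Where noncompliant participants agree, still draw the scheduled day 28 and 29 samples.
- Reconcile the noncompliance wording in the study design section: whether any or all of the items are needed, and what counts as missed supervision. Use the result to define the per-protocol set. Which rule is right is for the sponsor and investigators.

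The cost is analysis wording, one more model term, and follow-up for blood draws that are already scheduled. There are two downsides. The effect will be somewhat diluted if noncompliance is common, and one-period participants bring little precision (step 6), so the change guards against selection more than it recovers power.

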## Outcome measures

### Primary outcome

Serum LDL-C concentration and its change in response to PS consumption is considered the primary outcome of this trial. This outcome was chosen to measure plant sterol response in terms of lowering of the LDL-C concentration between the placebo and plant sterol consumption period. Blood samples (20 mL) will be collected on days 0, 1, 28, and 29 of the intervention period. The serum lipid profile (TC, LDL-C, HDL-C, and TG) will be measured using the Cobas 311 Analyzer (Roche Diagnostics GmbH, Mannheim, Germany). The average value for days 0 and 1 will be used as the baseline, and the average of days 28 and 29 will be the endpoint values.

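### Period-specific baseline LDL-C is measured and defined but has no place in the stated primary model: a possible loss of efficiency, not an error

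*Protocol article*

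**What the plan says.** In the protocol article, Study design schedules fasting blood on two consecutive days at the start and two at the end of each period. Primary outcome gives the first pair a name: "The average value for days 0 and 1 will be used as the baseline". The mean of days 28 and 29 is the endpoint value.

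Sample size calculation and statistical analysis then states the treatment effect as "comparing the endpoint values of the treatment and placebo periods, will be analyzed by the SAS MIXED procedure". The listed terms are sequence, sex, genoset and treatment-by-genoset as fixed factors, with participant as random and repeated. No baseline term and no period term is listed, and the section gives the defined baseline no role.

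The same section sizes the trial on a paired comparison of the two periods, "using the paired means statement to model the AB/BA crossover design (corr = 0.75, a = 0.05 and b = 0.80"), and concludes that "18 participants would be needed for each genoset to detect a response". The plan is "20–22 for each individual genoset".

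**The concern.** A baseline is defined under the primary outcome and then not used in the analysis of that outcome. In a crossover, the participant effect removes each person's stable LDL-C level. It does not remove a shift between one period and the other. The two endpoints are at least 49 days apart (28 days of treatment plus at least 21 of washout), whereas baseline and endpoint within a period are 28 days apart. If LDL-C is more alike within a period than across periods, the difference between the two baselines explains part of the difference between the two endpoints, and the model leaves that part in the error.

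Precision has consequences here. The Discussion classifies a genoset without a significant reduction as non-responding, so a wide interval can turn into a label. Slices are examined with Bonferroni correction: if there are three, power at n = 20 on the plan's own inputs falls from 84.4% to about 69%. Study design says recruitment difficulty forced the amendment, so adding participants is the expensive remedy.

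The unused baseline also leaves room for someone to analyse change from baseline, which can be much less precise than the endpoint comparison.

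**Working it through.** **Inputs, all from Sample size calculation and statistical analysis:** "an average reduction in LDL-C of 0.34 mmol/L resulting from PS consumption"; "the standard deviations in LDL-C for placebo (0.67 mmol/L) and PS (0.7 mmol/L"); "a correlation in LDL-C values of 0.75"; alpha 0.05. The 0.80 is written as b but used as power. Sidedness is not stated; two-sided reproduces the stated n. Period length and minimum washout are from Study design; the four-week washout is from Table 4.

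**1. The plan's own figure.**
SD of the paired difference = √(0.67² + 0.70² − 2 × 0.75 × 0.67 × 0.70) = √(0.4489 + 0.4900 − 0.7035) = √0.2354 = 0.485 mmol/L.
A two-sided paired t test (noncentral t) for 0.34 mmol/L has 80.0% power at n = 18, so the stated 18 is reproduced. Power is 84.4% at n = 20 and 88.0% at n = 22.

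**2. What a period baseline can add.** Let X1, X2 be the baselines and Y1, Y2 the endpoints of periods 1 and 2. Regressing Y1 − Y2 on X1 − X2 multiplies the variance by 1 − R². With equal variances and corr(Y1,Y2) = corr(X1,X2) = 0.75,

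R = [2·corr(X within, Y within) − corr(Y1,X2) − corr(X1,Y2)] / [2 × (1 − 0.75)].

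The document gives none of the three correlations in the numerator, so a range follows. One degree of freedom per genoset is charged for the covariate.

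*(a) All correlations 0.75.* R = (1.50 − 0.75 − 0.75)/0.5 = 0. No gain. Required n goes from 18 to 19; power at n = 20 goes from 84.4% to 84.2%.

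*(b) Exponential decay with time, scaled so that the two endpoints correlate 0.75.*

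| Washout | Within period (28 d) | Y1 with X2 (washout) | X1 with Y2 (whole trial) | R | R² |
|---|---|---|---|---|---|
| 21 d | 0.75^(28/49) = 0.848 | 0.75^(21/49) = 0.884 | 0.75^(77/49) = 0.636 | 0.1765/0.5 = 0.353 | 0.125 |
| 28 d | 0.75^(28/56) = 0.866 | 0.75^(28/56) = 0.866 | 0.75^(84/56) = 0.650 | 0.2165/0.5 = 0.433 | 0.188 |

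The SD falls from 0.485 to 0.454 (21 d) or 0.437 (28 d). Power at n = 20 becomes 88.6% or 90.8%; required n becomes 17 or 16.

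*(c) Decay plus day-to-day noise.* If two samples taken very close together would correlate only 0.90, R² drops to 0.05 (21 d) or 0.075 (28 d). At 0.80 it is about 0.01 in both cases.

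*(d) Higher correlation within a period only, all others held at 0.75.* R = (ρ − 0.75)/0.25, so ρ = 0.80, 0.85, 0.90 gives R² = 0.04, 0.16, 0.36 and power at n = 20 of 85.6%, 89.8%, 95.9%. The last is an extreme: it requires a correlation of 0.90 over 28 treated days but only 0.75 across a washout that may be shorter.

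**3. Change from baseline.** With equal variances, its variance relative to endpoints is 2 − 2R: 2.0 under (a), 1.29 or 1.13 under (b). Under (a), required n is 34 and power at n = 20 is 56%. It beats endpoints only when R exceeds 0.5, which among these scenarios happens only at ρ = 0.90 in (d).

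**4. Treatment-by-genoset test.** The plan does not power it. Assuming true effects of 0, 0.34 and 0.34 mmol/L with 20, 22 and 22 participants, the 2-df test has about 62% power. Scenario (b) raises this to about 68–71%.

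**5. Carry-over.** The period-2 baseline follows period-1 treatment. Suppose a residual effect λ on LDL-C remains at that baseline in those given PS first but has gone by day 28. With balanced sequences the mean PS-minus-placebo baseline difference is then λ/2, and adjustment shifts the estimate by slope × λ/2, making the reduction look larger. For an assumed λ of 0.10 mmol/L and slopes of 0.2 to 0.6, the shift is 0.01 to 0.03 mmol/L.

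**The case against.** The strongest case against is that nothing here is wrong. Primary outcome describes response as lowering between the placebo and PS periods, the model compares those endpoints, and the sample size rests on the same paired quantity. Outcome, analysis and power agree, and an endpoint-only crossover analysis is standard. All of that stands.

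The gain also depends on a figure the document lacks, and on its single value of 0.75 the gain is nil. That stands too. The time-distance argument must be applied to the washout as well: the end of period 1 may be only 21 days from the start of period 2, closer than the 28 days within a period. Scenario (b) does this, which is why the gain is modest.

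Two stronger readings are tempting. A reader might infer that adjustment is sure to narrow every genoset's interval at no cost; scenario (a) shows no gain and a small loss. A reader might also infer that adjustment protects against incomplete washout. The document does not say how any residual effect decays, and step 5 shows that adjustment can introduce a small bias where the endpoint comparison has none.

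Finally, covariate detail is often left to an analysis plan, and neither that plan nor the full protocol is shown; either may already give the baseline a role. But the article does not leave the model open. It names the response variable and the terms, so improving that stated choice is a fair comment.

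**Conclusion.** The point holds as one of efficiency. The stated model does not use the baseline the protocol defines, and it has no period term. The endpoint-only analysis is valid, agrees with the sample size calculation, and meets the plan's per-genoset power target before Bonferroni correction (84.4% at n = 20).

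The plausible benefit of adjustment runs from nil, if all correlations are 0.75, to a variance reduction of about 12–19% under time decay with a 21- to 28-day washout. Day-to-day noise pulls the latter towards nil. These figures rest on assumed correlation structures and equal variances, not on data in the document. Neither a guaranteed gain nor protection against carry-over is supported. The change is worth making because the data are already scheduled and the worst case costs little.

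**What to change.** Before unblinding, amend the model statement to:

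- include period as a fixed effect;
- include period-specific baseline LDL-C (mean of days 0 and 1) as a covariate in two parts: the participant's mean over both periods, and each period's deviation from that mean. The split keeps between-participant differences from distorting the within-participant slope;
- state that simple change from baseline is not the analysed variable;
- keep the unadjusted endpoint comparison as a sensitivity analysis, so that any effect of residual period-1 treatment on the period-2 baseline can be seen.

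If the baseline is meant only as a description, saying so would at least settle its role.

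The cost is model wording, one or two degrees of freedom and the small carry-over sensitivity above. No extra samples, visits or participants are needed.
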